**Methods:**

A multicenter, investigator-initiated randomized controlled trial (Clinical Trial Identifier number NCT05119608) including Intensive Care Unit (ICU)-treated COVID-19 survivors, who display symptoms of anxiety and/or depression at follow-up 12 months after hospitalization (Hospital Anxiety and Depression Scale ≥8 for depression or anxiety). Eligible individuals are referred to a psychiatrist for structured diagnostic assessment and inclusion in the trial. Participants will be randomized to either a 10-week cognitive behavioral therapy intervention with added acceptance and commitment therapy (CBT-ACT) or standard care (primary care referral). Primary study outcome measure is feasibility and patient adherence, defined as the proportion of participants who consent to randomization and remain in the study including follow-up. Secondary outcome measures include reduced symptoms in the HADS depression/anxiety subscales, post-traumatic symptoms, HRQoL and user satisfaction at 3 months after the intervention.

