### The Intervention

A structured, 10-session psycho-therapeutic intervention, typically occurring once weekly, will be performed (with a possibility to adjust the frequency). The therapy is based on cognitive behavioral therapy (CBT), with the addition of a therapeutic model of acceptance and commitment therapy (ACT) provided by clinical therapists with standard CBT training and extensive experience of complex mental health disorders. The intervention will be provided face-to-face whenever possible, with an alternative to offer the intervention online in case of practical difficulties or circumstances making an online meeting more convenient for the participant.

The control group (comparator) will consist of a referral to primary care (general practitioner) for medical assessment and support. The control condition is expected to provide at least the same level of support and care as in everyday, non-research-related, clinical care.

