### Outcomes

The primary outcome is to test if the psycho-therapeutic treatment approach is feasible in critically ill COVID-19 survivors at 12 months after ICU care, defined as the proportion of participants who consent to randomization and remain in the study including follow-up. Secondary outcome measures include reduced symptom burden in the HADS depression and anxiety subscales, post-traumatic symptoms and mental health-related quality of life (HRQoL), as well as users' experience and user satisfaction. Secondary outcome measures (Table 1) are included both in the 12-month assessment prior to randomization, as well as in repeated assessments at 3 months after randomization (2 weeks after treatment ending in the intervention group), 3 months after the completion of the intervention, and in a longer perspective (12 months after intervention/control), administered by an as outcome assessor blinded to the intervention arm. Participants' experience and satisfaction of the CBT-ACT intervention will be assessed 2 weeks after the intervention (for the randomized intervention group only).

**Table 1 T1:** Outcome assessments at baseline and follow-up.

**Outcome**	**Outcome assessment**	**Baseline variables**	**Study population 12 months post-ICU-care**	**Follow-up 2 weeks after intervention**	**Follow-up 3 months after intervention**	**Follow-up 12 months after intervention**
Mental health	Hospital Anxiety and Depression Scale (HADS)		X	X	X	X
	Post-Traumatic Stress Disorders Checklist for DSM-5 (PCL-5)		X	X	X	X
Fatigue	Modified Fatigue Impact Scale (MFIS)		X	X	X	X
Health related Quality of Life	SF-36-v2 (full scale and mental health sub-scale)		X	X	X	X
Participants' satisfaction	Satisfaction with Therapy and Therapist Scale (STTS)			X (intervention group only)		
Demographic background data	Age, gender	X				
Clinical baseline information	Severity of disease on arrival (Simplified Acute Physiology Score3, SAPS3)	X				
	Progression of disease severity in the ICU (30) including Sequential Organ Failure Assessment (SOFA)	X				
	Severity of ARDS on admission and daily,	X				
	Time (days) in the ICU	X				
	Invasive/non-invasive mechanical ventilation (yes/no)	X				
	Time on ventilator (days)	X				
Self-reported psychiatric information	Previous mental health disorders		X			

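### Follow-up visits are counted partly from randomisation and partly from the end of a therapy that controls do not receive, so time since randomisation can differ by arm at the later visits

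*Protocol article*

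**What the plan says.** **Visit schedule.** The Outcomes section of the protocol article places the first two follow-ups at "3 months after randomization (2 weeks after treatment ending in the intervention group), 3 months after the completion of the intervention". A third comes a year after what the text calls intervention or control, without saying which date that is for a control participant. In Table 1 the first follow-up column is headed "Follow-up 2 weeks after intervention". The other two columns are also counted from the intervention, and randomisation appears in none of the headings. Only the satisfaction row is limited to the intervention arm.

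**Therapy length.** The Abstract calls it a "10-week cognitive behavioral therapy intervention". The Intervention section describes "A structured, 10-session psycho-therapeutic intervention, typically occurring once weekly", but "with a possibility to adjust the frequency". The article gives no maximum duration.

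**Control arm.** "The control group (comparator) will consist of a referral to primary care (general practitioner) for medical assessment and support". No course length or end date is attached to this.

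**Which visit carries the outcomes.** The Abstract places the symptom and quality-of-life outcomes three months after the intervention, and Study Variables does the same for the SF-36v2 mental component score. That is visit 2.

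**The concern.** A between-arm comparison of symptoms is cleanest when both arms are measured at the same time since randomisation. Randomisation is the only date that every participant has, including anyone who stops therapy early. Here visit 1 has two definitions that can disagree, visit 2 is tied to an event that controls never reach, and visit 3 depends on a control reference point that is not defined. A change of pace or a late start moves the therapy-end dates in one arm only. If symptoms drift with time, for better or worse, that drift would be mixed into the arm difference.

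The mixed anchors also cause smaller ambiguities:

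- Study Variables restricts PCL-5 and MFIS at three months to participants who were positive at baseline. Visit 1 (from randomisation) and visit 2 (from completion) are both three-month visits.
- The Abstract lists satisfaction with the outcomes at three months after the intervention, whereas the Outcomes section and Table 1 put it at two weeks.

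**Working it through.** **Inputs from the article:** 10 sessions, nominally weekly over 10 weeks; visit 1 at 3 months from randomisation or 2 weeks after therapy end; visit 2 at 3 months after completion; visit 3 at 12 months.

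**Assumptions not in the article:** a fortnightly or twice-weekly pace, a 4-week start delay, and any control-arm reference date for visits 2 and 3.

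**Conversion:** 1 month = 365.25 / 12 / 7 = 4.35 weeks, so 3 months = 13.0 weeks and 12 months = 52.2 weeks.

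**Formula:** therapy end = start delay + pace × 9 (gaps from first to last session) or pace × 10 (weekly slots). The two counts give the ranges below. Visit 1 by therapy end = end + 2; visit 2 = end + 13.0; visit 3 = end + 52.2.

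**Step 1. The article's own equality (weekly, no delay).** End = week 9 to 10. Visit 1 = 9 + 2 to 10 + 2 = week 11 to 12, against week 13.0 from randomisation. The two definitions agree within about 1 to 2 weeks.

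**Step 2. Other paces and a late start (assumed).**

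| Scenario | Therapy end (week) | Visit 1 by therapy end | Minus 13.0 | Visit 2 | Visit 3 |
|---|---|---|---|---|---|
| Weekly, no delay | 9 to 10 | 11 to 12 | −2 to −1 | 22 to 23 | 61 to 62 |
| Weekly, 4-week delay | 13 to 14 | 15 to 16 | +2 to +3 | 26 to 27 | 65 to 66 |
| Fortnightly, no delay | 18 to 20 | 20 to 22 | +7 to +9 | 31 to 33 | 70 to 72 |
| Twice weekly, no delay | 4.5 to 5 | 6.5 to 7 | −6.5 to −6 | 17.5 to 18 | 57 |

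If visit 1 is instead held at week 13 for a fortnightly participant, sessions have taken place in weeks 1, 3, 5, 7, 9, 11 and 13, which is 7 of 10.

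**Step 3. Controls at visits 2 and 3.** The article gives no date, so two readings are tried.

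- *Counted from randomisation:* week 13.0 and week 52.2. Against the intervention arm at weekly pace, visit 2 differs by 22 − 13 to 23 − 13 = 9 to 10 weeks, and visit 3 by 61 − 52 to 62 − 52 = 9 to 10 weeks. At fortnightly pace the gap is 18 to 20 weeks. Under this reading a control's visit 2 would fall on the same date as visit 1, so it is less plausible for visit 2 than for visit 3.
- *Given a nominal 10-week end:* visit 2 at 10 + 13.0 = week 23. The arms then agree within about 1 week at weekly pace and differ by 8 to 10 weeks at fortnightly pace.

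**Step 4. Dates if everything is counted from randomisation.** 10 weeks = 10 / 4.35 = 2.3 months. The nominal schedule becomes 3 months, 2.3 + 3 = 5.3 months and 2.3 + 12 = 14.3 months, the same in both arms whatever the pace.

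**The case against.** A reader might infer that the plan does measure the arms at different times, that natural recovery would be credited to CBT-ACT, and that the primary outcome is compromised. The documents do not support any of these.

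- Visit 1 already has a common randomisation date, and its bracketed gloss nearly matches at the planned pace. The 13 weeks even leave a week or two for starting therapy.
- For visits 2 and 3 the control date is unspecified rather than shown to differ. The wording of visit 3 indicates that some control counterpart was intended.
- The fortnightly and delay figures show what could happen to an individual. The article does not say how many participants would change pace, so no mean difference between arms follows.
- The article gives no symptom trajectory for this period and stresses uncertainty about the long-term course. A faster pace would move intervention visits earlier, so the sign of any bias is open.
- The primary outcome is a single proportion consenting and staying in follow-up. It is not framed as a contrast between arms.
- The symptom outcomes are secondary in a pilot of at least 40, and the Abstract defers the question of benefit to a larger trial.

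All of this stands and limits the weight of the point. It is also fair that an article may leave visit windows and dropout rules to the full protocol. That argument does not cover the rule the article does state: visit 2, the comparison visit, is counted from completion of a therapy of adjustable length that one arm does not have, and text and table use different anchors. A control date in a fuller document would not remove the dependence on therapy pace in the other arm.

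**Conclusion.** The point holds in limited form. The anchors are inconsistent, and the stated rule lets time since randomisation differ by arm at the later visits; it does not establish that it will. At the planned pace with a prompt start, the inconsistency at visit 1 is worth 1 to 2 weeks. The larger gaps rest on assumptions: 7 to 9 weeks at visit 1 needs fortnightly therapy and use of the therapy-end anchor, and 9 to 10 weeks at visits 2 and 3 at weekly pace needs controls to be counted from randomisation. The direction of any bias is unknown. The effect falls on secondary outcomes; for the primary outcome, only the timing of the retention visits is touched. Correction is worthwhile because aim (c) still compares the arms on these outcomes and the results are meant to shape a larger trial.

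**What to change.** Count every between-arm symptom, fatigue and quality-of-life assessment, and the visits at which retention is judged, from the date of randomisation. Use the same windows in both arms and for participants who stop therapy early. Visits at about 3, 5.3 and 14.3 months keep the schedule that the nominal 10-week therapy implies. Tie only the satisfaction scale to therapy end. Then align the Abstract, the Outcomes text, Study Variables (including which three-month visit the PCL-5 and MFIS restriction refers to) and the Table 1 headings.

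The cost is a wording change, and therapy delivery is unaffected. The drawback is that some participants on a slower pace will be assessed before they finish therapy. That is consistent with the intention-to-treat approach stated under Data Analysis and Statistics.

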### Study Variables

Depression and anxiety will be measured using the HADS, a well-established instrument for the assessment of depressive and anxiety symptoms in clinical settings, and has demonstrated satisfactory sensitivity, specificity and validity (26). Mental health-related quality of life (HRQoL) measured as improved scores in the mental component summary score (MCS) from the SF-36v2 at 3 months after the intervention. The SF-36v2 has proven satisfactory psychometric characteristics in Sweden (31) and elsewhere (32). Post-traumatic symptoms will be assessed by the Posttraumatic Stress Disorder Checklist (PCL-5). The PCL-5 instrument has demonstrated satisfactory internal consistency and validity measures in the measure of post-traumatic symptoms (33). Fatigue will be studied using the Modified Fatigue Impact Scale (34), an abbreviated version of the longer, previous Fatigue Impact Scale, with demonstrated satisfactory validity and internal consistency (35). PCL-5 and MFIS will be assessed at 3 months only for participants who score positive at baseline on post-traumatic stress, and fatigue, respectively. User experience and satisfaction, in the intervention group only, will be assessed with the Therapy and Therapist Scale-Revised (STTS-R), a scale assessing both the aspects of the therapy method and the satisfaction with the therapist, and which has proved to have good measures of internal consistency and validity (36).

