## Methods

### Study Population and Setting

The present study will include individuals after intensive care, in two Swedish settings; four ICUs in the Skåne Region (southern Sweden) and two ICUs at Södersjukhuset (Region Stockholm). Surviving individuals admitted to ICU-care are invited to a structured follow-up after 12 months, including self-reported questionnaires regarding mental health problems. The 12-month follow-up measures are carried out through physical (or telephone) follow-up visits (Region Skåne) or through questionnaires sent by regular mail (Stockholm study site). COVID-19 survivors who screen positively for clinical anxiety or depression, defined as a score of ≥8 on either of the two sub-scales within the questionnaire HADS (26), are invited to take part in the study. Eligible individuals will then undergo a structured online clinical diagnostic assessment by a physician experienced in clinical psychiatry. The structured psychiatric medical assessment is guided by the Mini Neuropsychiatric Interview [MINI, (27)]. The MINI interview provides preliminary, structured diagnoses according to the diagnostic manual of the American Psychiatric Association, the DSM-5 [American Psychiatric Association, (28)]. The sections chosen for this assessment include those related to major depression, generalized anxiety disorder, and post-traumatic stress. In addition to the abbreviated MINI assessment, a non-structured clinical interview and broad diagnostic assessment will be performed.

After the assessment, eligible ICU survivors will be offered to enter the study. Consenting participants will be randomized on an equal basis (1:1) to the intervention or control arm. Randomization will be carried out from concealed, opaque envelopes, containing randomization or control assignment as based on a computer-generated randomization list [random.org, (29)], handled by a secretary not involved in the research project. Exclusion criteria, assessed upon the medical examination, include conditions in which participants are acutely suicidal, psychotic, suffering from a mental disorder requiring in-patient psychiatric treatment, opposed to receiving a psycho-therapeutic intervention, or with cognitive problems or language difficulties which are judged to be too extensive for the informed consent procedure and for a psycho-therapeutic intervention.

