### Data Analysis and Statistics

In addition to the comparison of the intervention and control conditions, respectively; multi-variable logistic regression model will be used to evaluate the associations between disease severity and socio-demographic variables and outcome measures. Study outcomes will be statistically controlled for a limited number of potentially confounding factors, including the presence of psychoactive medication in the participants' history, age, sex, and whether mechanical ventilation was applied during ICU treatment or not.

As the study includes feasibility as an outcome measure, and as the potential study group may expand in the future, the study sample is yet undetermined. For the feasibility measures, a preliminary aim is to include a convenience sample of at least 40 participants.

All analyses will be performed with an intention-to-treat approach for the total group and stratified for gender and age, since normative data suggest that females have more mental health problems than males, while older individuals have less problems than younger ones.

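### The rule limiting PCL-5 and MFIS at 3 months to baseline-positive participants contradicts Table 1, leaves the visit unclear and rules out a total-group analysis of both scales at that visit

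*Protocol article*

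**What the plan says.** Study Variables sets a selective rule for two of the symptom scales: "PCL-5 and MFIS will be assessed at 3 months only for participants who score positive at baseline on post-traumatic stress, and fatigue, respectively".

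The Outcomes section sets a general rule: "Secondary outcome measures (Table 1) are included both in the 12-month assessment prior to randomization, as well as in repeated assessments". It then lists three follow-ups: 3 months after randomisation (which it equates with 2 weeks after treatment ends in the intervention arm), 3 months after completion of the intervention, and 12 months after intervention or control. It names no subset of participants.

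Table 1 marks "Post-Traumatic Stress Disorders Checklist for DSM-5 (PCL-5") and "Modified Fatigue Impact Scale (MFIS") with a plain X at the pre-randomisation assessment and at each of the three follow-ups. The table does flag a restriction where one applies: the therapy-satisfaction row reads "X (intervention group only").

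Data Analysis and Statistics adds: "All analyses will be performed with an intention-to-treat approach for the total group and stratified for gender and age".

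Under Study Population and Setting, eligibility rests on HADS, "defined as a score of ≥8 on either of the two sub-scales within the questionnaire HADS (26), are invited to take part in the study". There is no entry threshold for post-traumatic stress or fatigue. Aim (c) under Specific Aims nonetheless includes both among the outcomes on which CBT-ACT is compared with standard care.

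**The concern.** The article gives two incompatible instructions about who receives PCL-5 and MFIS at one visit. A site following Table 1 would give them to everyone. A site following Study Variables would withhold them from some participants. A later analysis plan can choose an analysis set, but it cannot recover questionnaires that were never administered.

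If the selective rule is followed:

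- participants negative at baseline have no score at that visit, so the total-group analysis cannot be done there for these two scales;
- the population changes between visits, so a course over time would mix a selected group with the whole sample;
- new or worsening symptoms in baseline-negative participants go unseen at that visit;
- the estimates handed on to the larger trial that the article foresees would, at that visit, come from a group selected for high baseline scores and would be less precise.

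The visit itself is also unclear, because the Outcomes section contains two time points that could be called 3 months.

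**Working it through.** The article states no power, effect size or SD for these outcomes, so there is no planned figure to reproduce. The check is mainly a comparison of the texts, with an illustration of size.

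**1. Who is assessed**

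| Source | PCL-5 and MFIS at follow-up |
|---|---|
| Outcomes text | all Table 1 secondary outcomes repeated, no subset |
| Table 1 | X at 2 weeks, 3 months and 12 months after intervention, no restriction |
| Study Variables | at 3 months, baseline-positive participants only |
| Data Analysis and Statistics | all analyses, total group, intention-to-treat |

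The first two rows agree and the third conflicts with them. An unmarked restriction in Table 1 is an unlikely explanation, because the table marks the one for the satisfaction scale.

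**2. Can baseline-negative participants be in the trial?** Yes. Entry needs HADS ≥8 on either subscale and nothing on PCL-5 or MFIS. Unless every HADS-positive participant is also positive on both scales, the restriction removes randomised people from at least one of the two analyses.

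**3. Which visit?** In the Outcomes section, 3 months after randomisation is the visit that Table 1 labels 2 weeks after intervention. Three months after completion is a separate visit. The abstract places the secondary outcomes at 3 months after the intervention, and Study Variables uses that time point for the SF-36v2 mental component score. The later visit is therefore the more natural reading, but the restricting sentence does not say so.

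**4. Size (illustration)**

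Inputs: 40 participants (the article's minimum aim), allocation 1:1, no dropout. The share positive at baseline is not given for HADS-positive participants. The Introduction reports 33-36% for depression, anxiety and post-traumatic stress in survivors of critical COVID-19 at a median of 5 months. That is a different population, and the figure does not cover fatigue. A range of 35-60% is assumed here.

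Number per arm: 0.35 × 40 = 14, or 7 per arm; 0.60 × 40 = 24, or 12 per arm; all participants, 20 per arm.

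Half-width of the 95% confidence interval for a difference in means, in SD units: t(0.975, 2n − 2) × √(2/n).

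- n = 20: 2.024 × 0.316 = 0.64
- n = 12: 2.074 × 0.408 = 0.85
- n = 7: 2.179 × 0.535 = 1.16

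Relative to full assessment, the interval is 0.85/0.64 = 1.3 to 1.16/0.64 = 1.8 times as wide. The normal approximation, 1.96 × √(2/n), shows the same pattern: 0.62 at n = 20 and 1.05 at n = 7. If a larger share were positive the loss would be smaller: at 70% (14 per arm) the normal approximation gives 0.74.

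**The case against.** Several points on the other side are sound.

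- **Scope.** A reader might infer that post-traumatic stress and fatigue can never be analysed in the randomised population. The text does not support that: the restriction is stated for 3 months only, and the remaining visits, including 12 months, are unrestricted.
- **Validity.** A reader might infer that the comparison at the restricted visit is biased. It is not. Positivity is determined before randomisation, so arms compared as allocated within that subset form a fair comparison. Regression to the mean would exaggerate improvement within each arm, but it affects both arms alike, and the article plans a comparison between arms.
- **Intention-to-treat.** The reference to the total group is paired with stratification by gender and age, so it can be read as overall versus strata. Analysis by allocated arm in a subset defined before randomisation is compatible with intention-to-treat. This weakens the conflict with the statistics section. It leaves the conflict with the Outcomes text and Table 1 untouched, and a baseline-negative participant still has no score to analyse at that visit.
- **Design choice.** Following a symptom scale only in those who have the symptom can be defended when the aim is to relieve symptoms. It would then have to be shown in the schedule and carried into the analysis set, which the article does not do.
- **Cut-off.** The definition of positive may stand in the full protocol. Its absence from a condensed article is not part of this point.
- **Importance.** These are secondary measures in a feasibility pilot, the abstract leaves the question of symptom improvement to a larger trial, and no precision is promised for them. Fatigue appears in aim (c) and Table 1 but not in the running list of secondary outcomes. This lowers the severity but does not remove the contradiction.

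**Conclusion.** The contradiction is real and confined to one visit and two secondary scales. As written, the Study Variables rule cannot stand alongside the Outcomes text and Table 1, and under it a total-group analysis of PCL-5 and MFIS at that visit is impossible. Which of the two candidate visits is meant is not stated. What is lost is coverage, comparability across visits and precision. Randomisation and the primary outcome, consent and retention, are not affected.

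The precision figures depend on the assumed 35-60% positive share, on exactly 40 participants with no dropout, and on applying one share to both scales. The article supports none of these firmly, so they show the order of magnitude only. This is a point that should be fixed, ideally before follow-up data are collected; it does not threaten the trial's main purpose.

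**What to change.** Preferred: delete the restricting sentence in Study Variables. Give PCL-5 and MFIS to all randomised participants at every follow-up, as Table 1 already shows. Analyse all of them by allocated arm with adjustment for the baseline score, and report the baseline-positive group as a labelled subgroup.

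If the restriction is kept: mark it in the PCL-5 and MFIS rows of Table 1, state which of the two 3-month visits it covers, and name the baseline-positive set as the analysis population for those scales at that visit, as a stated exception to the total-group rule in Data Analysis and Statistics.

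The preferred change alters one sentence and adds at most two self-report questionnaires for some participants at one visit, so the downside is a small respondent burden. The ethics statement lists approved amendments, so this change may need one too.
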